#### Specific aim 3—interventions and comparisons

Consistent with the EPIS Implementation phase, the research team will pilot-test the AAR implementation strategy on improving CFT outcomes and explore team mechanisms. Specifically, to test the effectiveness of the AAR on improving outcomes associated with the CFT services intervention, we will implement randomization with parallel assignment in two CWS system regions, at the caseworker level. In each region, four CWS caseworkers will be followed as they engage in 5 CFT meetings (8 CWS caseworkers total). Within each region, two of the CWS caseworkers will be assigned to the team-enhanced implementation strategy, CFT + AAR (4 CWS caseworkers total), and two CWS caseworkers will be assigned to the standard implementation, CFT as usual (4 CWS caseworkers total). CFT as usual consists of CFT Meeting Facilitation wherein a mental health services organization partners with CWS to schedule the CFT meetings. The research team will utilize blocked randomization of CWS caseworker to intervention condition (CFT + AAR or CFT as usual) to ensure equal group sizes. As such, assignment of condition will be implemented by the research team without concealment or blinding.

Child mental health concerns are identified by a preliminary administration of the Child & Adolescent Needs & Strengths (CANS) [55] assessment for children aged 6–17 by the CWS caseworker at the initial family visit, which typically occurs 2–3 weeks prior to the initial CFT meeting. Based upon this initial visit and preliminary CANS results, informal and formal support persons are invited to the CFT meeting by the CFT Meeting Facilitation program. The CANS results are an integral component of the initial CFT meeting, during which the CWS caseworker guides discussion around the mental health needs that emerged from the initial CANS assessment and finalizes the Action Plan to attend to these needs. In addition to the above, those in the CFT + AAR will be guided through the AAR team effectiveness intervention, as facilitated by research staff, immediately following the CFT meeting. To optimize assessment of mental health services linkage, only CFTs which include a child with an identified mental health service determined by the preliminary administration of the CANS assessment by the CWS caseworker at the initial family visit will be included.

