Immediately upon completion of each of the 5 CFT or CFT + AAR team meetings, the CWS caseworkers together with ~ 7 additional CFT members will provide data a via web-based online survey to assess mechanisms and outcomes. This results in 8 caseworkers leading 5 CFTs each for a total of 40 unique CFTs. Each of the 40 CFTs has ~8 participants, for a minimum total of 320 data points. See Fig. 2 for sampling.

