### Analytic plan

Multilevel modeling with random intercepts and slopes will be used to examine differences in the targeted outcomes between CFT and CFT + AAR conditions, while accounting for the nested data structure. Specifically, this project will test the main effect of the AAR on implementation outcomes and child/family outcomes. Analyses will include the between-CFT meeting factor of condition (CFT vs. CFT + AAR) and within-CFT meeting factor of individual CFT member participant. The cross-level condition by participant interaction effect on the specified outcomes will be of primary interest.

A cross-level prediction model will test the extent to which the condition effect on the CFT outcomes is mediated by its proximal effect on team processes and emergent states. To assess the extent to which team processes are targeted by the AAR intervention, the Goal and Task subscales of the Working Alliance Inventory-Short Revised (WAI-SR) will be used to assess goal specification and strategy formulation, respectively [60, 63]. The Collaboration subscale of the Collaboration & Satisfaction About Care Decisions (CSACD) [57] measure will be used to assess the extent to which the AAR engages the team processes of communication and coordination. Several measures will be used to assess the extent to which emergent states are targeted by the AAR. Specifically, the Bond subscale of the WAI-SR and the McAllister Affect-Based Trust [58] measure will be used to assess trust. Edmondson’s Psychological Safety Climate [41] measure will assess the extent to which the AAR impacts the emergent state of psychological safety. To assess the extent to which the AAR engages the emergent state of shared mental models, a card-sorting task will assess CFT team shared mental models by examining perceptions of member roles, responsibilities, and goals across CFT team members. The concepts contained in the card sort will be representative of specific CFT roles, task responsibilities, and goals. To determine the feasibility, acceptability, and appropriateness of the AAR for CWS CFTs, those in the CFT + AAR condition will complete the Feasibility, Acceptability, and Appropriateness of Intervention Measures, respectively [51].

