### Power analysis

Based upon the sampling strategy, power analysis was conducted to inform the detectable magnitude of effect. Power for the primary CFT services intervention outcomes, and team processes/emergent states outcomes, was estimated using a multi-step approach recommended by Hox [64]. First*,* a total number of observations was computed while ignoring nesting. With 8 team members from 8 child-family teams (4 per region) participating in data collection following each of 5 child-family team meetings, there is a total of 320 observation results. For these observations, the nested data structure introduces dependency that decreases the level of statistical power. To adjust for this, a second step was to penalize the total sample for nesting. This was accomplished using a reorganization of the design effect formula (i.e., *n*_*eff*_ = *n*/[1 + [*n*_*clus*_ − 1]*ρ*]), which provides the effective sample size of independent observations. Using conservative nesting effects for CFT members within CFT meetings, *ρ* = 0.20, the 320 observations provide statistical power equivalent to 36 independent observations. Third, the effective sample size was used to perform conventional, single-level power analysis using GPower. Assuming power of 0.80 and *α* = 0.05, results indicated that a small-to-medium main effect of *f*^2^ = 0.10 for condition on CFT clinical intervention outcomes may be detected. As noted, for the preliminary mediation tests, statistical power is necessarily limited. Simulations performed by Fritz and MacKinnon [65] have demonstrated that required sample sizes for mediated effects range from 35 to 74. This depends on the magnitude of the effects for the respective paths, with the smaller sample sufficient if both paths have large effects and the larger sample sufficient if both paths have medium effects. As such, the effective sample size of 36 is potentially sufficient if the magnitude of each effect for the respective paths is great.

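### Caseworkers are randomised, but condition is specified between CFT meetings and no caseworker level is named, so the main-effect test fitted as written can be anti-conservative

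*Protocol article*

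**What the plan says.** Under Specific aim 3 the unit of randomisation is explicit: "we will implement randomization with parallel assignment in two CWS system regions, at the caseworker level". Each region contributes four caseworkers, two per arm, so the trial compares four with four. On meetings: "This results in 8 caseworkers leading 5 CFTs each for a total of 40 unique CFTs". On respondents: "Each of the 40 CFTs has ~8 participants, for a minimum total of 320 data points".

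The Analytic plan opens with a general commitment, "Multilevel modeling with random intercepts and slopes will be used to examine differences in the targeted outcomes", and adds that the nested structure will be accounted for. It then gives the factors: "Analyses will include the between-CFT meeting factor of condition", and below it the "within-CFT meeting factor of individual CFT member participant". It says a main effect of the after-action review (AAR) will be tested, and that the cross-level condition-by-participant interaction is of primary interest.

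The Power analysis applies a design-effect penalty with a correlation of 0.20, introduced as follows: "Using conservative nesting effects for CFT members within CFT meetings". It arrives at 36 effective observations and a detectable main effect of condition of f² = 0.10. Neither section names a caseworker random effect or degrees of freedom based on caseworkers.

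**The concern.** All five meetings of a caseworker fall in the same arm, so condition varies only between caseworkers. The caseworker guides the discussion, finalises the Action Plan and completes the survey after each meeting. Ratings of alliance, engagement and satisfaction from one caseworker's meetings may therefore resemble each other more than ratings from different caseworkers' meetings.

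A model whose highest cluster is the meeting treats 40 meetings as independent replicates of the condition. If caseworkers differ, its standard error for the main effect is too small and its degrees of freedom too many. An apparent AAR effect could then reflect only which four caseworkers were allocated to that arm. This matters because the main effect is both tested in the Analytic plan and the effect for which the study is powered.

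**Working it through.** **1. Reproduce the plan's effective sample size.** The formula is n_eff = n / [1 + (n_clus − 1)ρ], with n = 320 and ρ = 0.20 from the Power analysis.

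- Members within a meeting, the nesting the text names (n_clus = 8): 320 / (1 + 7 × 0.20) = 320 / 2.4 = 133.
- n_clus = 40: 320 / (1 + 39 × 0.20) = 320 / 8.8 = 36.4, the stated 36.
- n_clus = 5 gives 320 / 1.8 = 178.

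Only 40 reproduces the stated figure. Forty is the number of observations per caseworker (5 × 8), and also the total number of meetings. The stated label and the arithmetic do not agree.

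**2. Degrees of freedom.** Meeting level: 40 − 2 = 38. Caseworker level: 8 − 2 = 6, or 5 with a region term.

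**3. Standard errors.** Set total variance to 1 and the within-meeting correlation to 0.20 (from the Power analysis). Let c be the part of that 0.20 due to caseworker. The document gives no c, so it is assumed and varied from 0 to 0.20.

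- Variance of a meeting mean: 0.20 + 0.80/8 = 0.30.
- True variance of the arm difference: 2 × [c/4 + (0.30 − c)/20].
- Expected mean square within arms when caseworker is ignored: [16(0.30 − c) + 3(0.30 − c + 5c)] / 19. The model variance of the difference is 2/20 of this.

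At c = 0.05, the true variance is 2 × (0.0125 + 0.0125) = 0.050, so SE 0.224. The model's mean square is (4.0 + 1.5)/19 = 0.289 and its variance 0.0289, so SE 0.170. The ratio is 0.76.

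**4. Type I error.** In each simulated null trial (200,000 per value of c; 4 vs 4 caseworkers, 5 meetings each, 8 members each; region not modelled), a t test on 40 meeting means was compared with a t test on 8 caseworker means. With balanced data the first is equivalent to the two-level model.

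| Caseworker ICC (assumed) | Model SE / true SE | Meeting-level test, nominal 5% | Caseworker-level test |
|---|---|---|---|
| 0 | 1.00 | 5.0% | 5.0% |
| 0.02 | 0.88 | 8.2% | 4.9% |
| 0.05 | 0.76 | 13.2% | 5.0% |
| 0.10 | 0.63 | 21.1% | 5.0% |
| 0.20 | 0.48 | 34.4% | 5.0% |

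A separate simulation of 40,000 trials gave 5.1%, 8.4%, 13.0%, 21.1% and 34.5% for the meeting-level test.

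**5. The interaction.** In a contrast of four members against four within each meeting, a shared caseworker intercept cancels. Ignoring caseworker, that test rejected 4.7%, 4.9%, 5.2% and 5.1% at c = 0, 0.05, 0.10 and 0.20. If the contrast is instead caseworker against other members, the same person supplies one side of it in all five meetings. If a stable rater component is 0.10 to 0.20 of total variance (assumed), the meeting-level test rejects roughly 10 to 16%.

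**6. Detectable main effect at caseworker level.** With 6 df, two-sided α = 0.05 and 80% power, the difference must be about 3.37 standard errors. With f² = d²/4, c = 0.05 gives d = 3.37 × 0.224 = 0.75 and f² = 0.14. At c = 0.02, 0.10 and 0.20, f² is about 0.11, 0.20 and 0.31.

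**The case against.** The best defence is that the plan never says the model has only two levels. It commits to multilevel modelling that accounts for nesting, the Fig. 2 note lists caseworker in the sampling structure, and a condensed article may leave the list of random effects to a statistical analysis plan. It is also literally true that condition differs between meetings and not within them. This stands in part: a reader might infer that a caseworker term has been ruled out, and the text does not show that. However, the article does specify the level of the condition factor, and that level is not the randomised one. A general reference to nesting does not supply the missing level.

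A second defence is that 36 follows from a cluster of 40, so caseworker clustering was considered. That is possible. The Fig. 2 note and the Power analysis also speak of eight teams followed over five meetings, and on that reading team and caseworker coincide. But Specific aim 3 has 40 unique CFTs, the correlation is labelled as members within meetings, and a penalty in the power calculation does not correct the standard errors of the analysis.

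Third, the interaction, not the main effect, is called primary. This limits the point: the inflation in the table must not be carried over to the interaction.

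Two further readings go too far. The 34–35% figure is not implied by the plan's 36; it requires all the within-meeting correlation to come from caseworkers. Nor does the absence of a region term create false positives; leaving out a balanced stratum tends to be conservative.

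**Conclusion.** The concern holds for the condition main effect if the model is fitted at the levels the article names. Caseworkers are the randomised units, yet condition is placed between meetings, and the power section's label disagrees with its own arithmetic. The size depends on a caseworker correlation the document does not give: no inflation at 0, about 8% at 0.02, 13% at 0.05, 21% at 0.10, and 34–35% only at the limit. These figures assume balanced continuous outcomes and a total within-meeting correlation of 0.20. Actual inflation is therefore conditional, but with four caseworkers per arm even a modest correlation matters. The Specific aim 3 section calls the study a pilot test but also says it tests effectiveness, so the pilot label does not remove the need for a valid error term.

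**What to change.** - State the structure as members within CFT meetings within caseworkers, with a caseworker random intercept. For the interaction, let member effects vary by caseworker where that can be estimated.
- Test condition with Kenward-Roger or Satterthwaite degrees of freedom, or on caseworker-level summaries. The two agree exactly only for balanced continuous data, and about eight respondents per meeting will not be perfectly balanced.
- For service linkage, which is recorded per child from administrative data, use child (or CFT) within caseworker.
- Include region because it is the randomisation stratum, at a cost of 1 df, and not as a remedy for false positives.
- Do not make a re-randomisation test the primary test. There are C(4,2)² = 6 × 6 = 36 allocations, so the smallest two-sided p is 2/36 = 0.056.
- Reconcile the clustering unit across Specific aim 3 (40 unique CFTs), the Fig. 2 note and Power analysis (eight teams over five meetings), and the Analytic plan.
- Restate the detectable effect on caseworker-level degrees of freedom, with the assumed caseworker correlation shown as a range.

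No new data are needed. The cost is wider intervals and a less favourable detectable effect: about f² = 0.11 to 0.31 for caseworker correlations of 0.02 to 0.20 on 6 df, and slightly more on 5, against the stated 0.10.

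### The analytic plan names neither region, the randomisation stratum, nor caseworker, the randomised unit, among its model terms; both need to be stated for the test of condition to match the randomisation.

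*Protocol article*

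**What the plan says.** Specific aim 3 sets the randomisation out clearly: "we will implement randomization with parallel assignment in two CWS system regions, at the caseworker level". There are eight caseworkers, four to a region, and each is observed over five meetings. On allocation the section states: "Within each region, two of the CWS caseworkers will be assigned to the team-enhanced implementation strategy"; the other two work as usual. It adds that "The research team will utilize blocked randomization of CWS caseworker to intervention condition"; the reason given is equal group sizes. Region is therefore a stratum, balanced exactly 2:2, and the caseworker is the unit randomised.

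The Analytic plan says "Multilevel modeling with random intercepts and slopes will be used to examine differences in the targeted outcomes" and promises to do this "while accounting for the nested data structure". It does not list the levels. It then names two model factors: "Analyses will include the between-CFT meeting factor of condition", and the individual participant within the meeting. It plans a test of the main effect of the AAR and calls the interaction of condition with participant the effect of primary interest.

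The Power analysis mentions region only when counting observations ("there is a total of 320 observation results") and has no region term.

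**The concern.** An analysis should reflect how units were allocated. Two features of this allocation do not appear among the named model terms, and they act in opposite directions.

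- **Region.** With 2:2 allocation in each region, a regional difference cancels from the condition estimate. If region is not modelled, that difference stays in the error variance, so the standard error is larger than the design warrants.
- **Caseworker.** Condition varies only between caseworkers. Calling it a between-meeting factor invites a test against variation between 40 meetings rather than between 8 caseworkers, which makes the standard error too small.

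With only 8 randomised units, either choice can change the conclusion about condition, and a choice made after seeing the data would be hard to defend.

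**Working it through.** **Inputs from the protocol.** 8 caseworkers, 2 regions, 2:2 in each; 5 meetings per caseworker; about 8 members per meeting; 320 observations; intraclass correlation 0.20; alpha 0.05 (two-sided assumed). **Not given:** the regional difference D and the caseworker variance. Both are varied below.

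**The plan's own figure.** n_eff = n/[1 + (n_clus − 1)ρ] = 320/(1 + 39 × 0.20) = 36.4. This gives the stated 36 only with n_clus = 40, the 5 × 8 observations belonging to one caseworker. With the 8 members of one meeting, to which the 0.20 is said to refer, it is 320/(1 + 7 × 0.20) = 133. So the power section in effect clusters by caseworker, while the model text speaks of meetings. (The stated f² = 0.10 does not follow from n = 36, where two-sided power is 45%; that is a separate matter.)

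**Case A: caseworker is a level, region omitted.** Compare 8 caseworker means, 4 v 4. Let σ² be the within-region variance of a caseworker mean.

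- Without region: 6 df, expected error variance σ² + D²/3 (the regional sum of squares is 8 × (D/2)² = 2D², spread over 6 df).
- With region: 5 df, error variance σ².
- Critical t: 2.447 on 6 df, 2.571 on 5 df.

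Break-even on expected squared interval width: 2.447²(σ² + D²/3) = 2.571²σ², so D = √{3[(2.571/2.447)² − 1]} σ = 0.56σ. Region then makes up 1 − (2.447/2.571)² = 9.4% of the unadjusted error variance. Measured as (D²/4)/(D²/4 + σ²), the share used in the first table, the same point is 0.078/1.078 = 7%.

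To express this in outcome SDs, put the whole 0.20 at caseworker level (assumption): σ² = 0.20 + 0.80/40 = 0.22, and D = 0.56 × √0.22 = 0.26 outcome SD.

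Simulated results, effect 2.2 SD of caseworker means (the SD includes the regional part):

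| Regional share | Type I without region | Power without | Power with |
|---|---|---|---|
| 0% | 5.0% | 74% | 70% |
| 10% | 3.9% | 73% | 75% |
| 30% | 2.0% | 72% | 84% |

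At 30% the interval is 17% narrower with region. A 30% share needs D = √(4 × 0.3/0.7) = 1.31σ, or 1.31 × √0.22 = 0.61 outcome SD.

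At the plan's own effect, f² = 0.10, d = 2√0.10 = 0.63 outcome SD, with σ² = 0.22:

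| D (outcome SD) | Mean 95% interval width, without → with region | Power, without → with region |
|---|---|---|
| 0 | 1.56 → 1.62 | 36% → 34% |
| 0.2 | 1.60 → 1.62 | 34% → 34% |
| 0.3 | 1.66 → 1.62 | 32% → 34% |
| 0.5 | 1.83 → 1.62 | 25% → 34% |
| 1.0 | 2.51 → 1.62 | 8% → 34% |

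**Case B: caseworker is not a level, condition tested between 40 meetings (38 df).** Worked example with D = 0, caseworker component 0.05 and meeting component 0.20 (assumptions):

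- Variance of a meeting mean within a caseworker: 0.20 + 0.75/8 = 0.294.
- True variance of the condition difference: 2 × (0.05/4 + 0.294/20) = 0.0544.
- Variance the meeting-level test uses: 2 × [16 × 0.294 + 3 × (0.294 + 5 × 0.05)]/38 = 0.333, then 0.333/10 = 0.0333.
- Standard error understated by a factor √(0.0333/0.0544) = 0.78.

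Simulated type I error (meeting component 0.20 in the first two rows, 0 in the third):

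| Caseworker ICC | D = 0 | D = 0 with region added | D = 0.5 | D = 1.0 |
|---|---|---|---|---|
| 0.05 | 12% | 12% | 9% | 4% |
| 0.10 | 18% | 18% | 15% | 8% |
| 0.20 | 35% | 36% | 29% | 19% |

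**The case against.** The strongest reply is that this is silence, not exclusion. The plan promises to account for nesting, never says that the two named factors are the only terms, and an article may leave a stratum term to a fuller document. That stands to this extent: nothing shows that region or caseworker will be left out. But the text does more than stay general. It names the model factors and places condition between meetings, and that description does not carry through the allocation in Specific aim 3.

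A reader might infer that the intervals for condition are simply too wide and power is lost. The documents do not support this. No regional difference is reported, the two regions belong to one county system, and if they are alike the omission gains slightly. On a literal reading without a caseworker level, the intervals are generally too narrow instead.

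Two further points stand. A regional shift in level largely cancels from a contrast within meetings, so the Case A loss concerns the condition main effect, not the interaction with participant. And this is a pilot test: at the plan's own effect size, power on caseworker means is about a third even with region in the model.

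**Conclusion.** The point holds as a mismatch between the described randomisation and the described model, with a consequence that is conditional in size and direction. With caseworker as a level, leaving out region makes the main-effect test conservative only beyond a regional difference of about 0.26 outcome SD. That threshold rests on an assumed caseworker-mean variance of 0.22. The largest gains from adjustment (9 points of power at 0.5 SD, 26 at 1.0 SD) require differences that the documents neither give nor rule out. Without a caseworker level, the more serious fault is a type I error well above 5% at the assumed correlations, unless the regional difference is large enough to mask it. Stating region alone is therefore not enough. The estimate of the condition main effect is not biased by omitting region, since allocation is balanced.

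**What to change.** In the Analytic plan, state that the models for condition include region as a two-level fixed effect and caseworker as a random level above meeting. State also that the condition main effect is tested against between-caseworker variation with 8 − 3 = 5 df. Describe condition as a between-caseworker factor. Both parts are needed, and both should be fixed before outcome data are seen.

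The cost is a sentence or two of wording and 1 of 6 df. If the regions do not differ, that means an interval about 4% wider and about 2 to 4 points less power. Compared with a meeting-level test, intervals will be wider, but they will reflect the 8 units actually randomised.

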## Mechanistic model and how AARs will improve child/parent outcomes

This project aims to leverage and apply knowledge from the field of team effectiveness research to improve CWS child/family outcomes. Specifically, the proposed project will enhance the current CFT services intervention with an evidence-based team development intervention (i.e., AARs) to improve the mechanisms of team processes and team emergent states for CFT members (including CWS caseworkers and children/families), resulting in enhanced service/clinical outcomes (i.e., specialty mental health services linkage).

The AAR team development intervention, hereafter referred to as CFT + AAR, is hypothesized to improve outcomes associated with the CFT meeting services intervention through enhanced team processes and emergent states. See Fig. 1 for the proposed mechanistic model and Table 1 for the proposed measures for model constructs. The AAR aims to boost emergent states of stronger shared mental models amongst team members (Cognition), and greater levels of trust and psychological safety amongst team members (Affect). Additionally, the AAR intends to improve team processes of communication and coordination (Actions) and positive perceptions of the specified goal and formulated strategy for the CWS child/family Action Plan (Transition). By enhancing the mechanisms of emergent states and team processes, the AAR facilitates improved fidelity and child/family outcomes. Specifically, CFT meeting fidelity is exemplified when child/family voice and shared decision-making amongst team members is present. When CFT meeting fidelity is enhanced, greater satisfaction with the child/family Action Plan may be achieved, ultimately resulting in successful specialty mental health services linkage.

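### The effect named as of primary interest is a condition-by-participant interaction, whereas the hypothesis, the stated test, the mediation model and the power statement all concern the condition effect

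*Protocol article*

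**What the plan says.** The Analytic plan opens with "Multilevel modeling with random intercepts and slopes will be used" and then says "this project will test the main effect of the AAR on implementation outcomes and child/family outcomes". It defines the two factors as the "between-CFT meeting factor of condition (CFT vs. CFT + AAR) and within-CFT meeting factor of individual CFT member participant". The next sentence reads "The cross-level condition by participant interaction effect on the specified outcomes will be of primary interest". The mediation model in the following paragraph starts from the effect of condition on the outcomes.

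Elsewhere, the section on the mechanistic model says that CFT + AAR "is hypothesized to improve outcomes associated with the CFT meeting services intervention through enhanced team processes and emergent states". The Power analysis, "Assuming power of 0.80 and *α* = 0.05", concludes that "a small-to-medium main effect of *f*^2^ = 0.10 for condition on CFT clinical intervention outcomes may be detected". Specific aim 3 randomizes eight caseworkers, four to each condition, in parallel groups.

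**The concern.** A main effect and an interaction are different estimands, and the paragraph commits to the first and then gives primacy to the second. The interaction measures how unequal the AAR effect is across members. A benefit shared by all members, the simplest form of success under the hypothesis, would leave the primary result null. Benefit to some members offset by harm to others could make it significant with no average effect. With both effects named in one paragraph, it would also be open after the data are seen which of them counts as the main result.

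A second difficulty is the wording of the participant factor. Taken as the individual person, it is nested in condition, so the interaction may have nothing to estimate.

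**Working it through.** **1. The statements side by side**

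| Place | Effect concerned |
|---|---|
| Mechanistic model (hypothesis) | condition, acting through team processes and emergent states |
| Analytic plan, second sentence | main effect of the AAR |
| Analytic plan, fourth sentence | condition × participant, of primary interest |
| Analytic plan, mediation | condition effect |
| Power analysis | main effect of condition |

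Four of the five concern condition. No section hypothesizes a difference between members.

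**2. The plan's power figure**

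The plan uses n_eff = n / [1 + (n_clus − 1)ρ], with n = 320 and ρ = 0.20. Setting n_clus = 40 gives 320/8.8 = 36.4, which reproduces the stated 36. At N = 36 with one tested predictor, f² = 0.10 has power of 45% two-sided (58% one-sided), so the stated f² at 80% power does not reproduce. That is a separate matter and nothing below depends on it. What matters here is that the calculation is for a condition main effect and that no interaction is powered.

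**3. A uniform benefit**

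Let the AAR raise the mean by δ for every kind of member. Each interaction contrast is then δ − δ = 0. The primary test rejects with probability α = 0.05 whatever the value of δ.

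**4. Estimability if the factor is the individual person**

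The fixed-effect design matrix is [1, person, condition, person × condition]. If nobody appears in both arms, the condition column is the sum of the person indicators in one arm. Each product column is either zero or a copy of a person indicator. The ranks under the two descriptions of the sample are:

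- Specific aim 3, 40 unique CFTs, assuming only caseworkers recur: 40 × 7 + 8 = 288 people. The rank is 288 with person alone, with condition added, and with the interaction added.
- Figure 2 note and Power analysis, 8 teams surveyed after 5 meetings: 8 × 8 = 64 people. The rank is 64 in all three cases.

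The interaction has 0 degrees of freedom under both descriptions. With one survey per person per meeting, a random slope for person within a meeting cannot be separated from residual error. A random slope for condition within caseworker or CFT cannot exist, because condition does not vary there.

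**5. Estimability if the factor is role**

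Assume eight roles, all present in both arms. The ranks are 8 (role), 9 (adding condition) and 16 (adding the interaction), so the interaction has 7 degrees of freedom. If that interaction had f² = 0.10 (an assumption), its power would be about 17% at an effective sample of 36, 73% at 133 (n_clus = 8) and 99% at 320. The protocol does not say which effective size suits a within-meeting contrast, so its power is unknown.

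**6. Outcomes where the interaction has no meaning**

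Service linkage comes from administrative data on the child. It has one value per child and cannot vary across the members of a CFT. Table 1 shows the feasibility, acceptability and appropriateness measures for CFT + AAR only, so they allow no comparison by condition. The sentence on primary interest excepts none of these.

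**The case against.** The best defence is that the participant factor was meant as member type. The Participants section lists four types of participant, and a factor that varies within meetings and crosses condition is naturally a type. A differential effect would also be coherent with the remark that children and family may feel least comfortable taking part. Coding of the factor can be left to an analysis plan. This stands in part: a reader might infer that the interaction cannot be estimated at all, and the document does not support that. Non-estimability holds for the literal wording, and a professional who attended meetings in both arms would be an exception even there. The defence does not make the interaction the hypothesized or powered effect.

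The defence can add that the main effect is still promised and powered, in what is called a pilot test. That is right. The analysis would not be lost; the fault lies in which effect carries the primary inference.

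A reader might also infer that a role interaction must be the less precise test. That does not follow. Take two parents or caregivers among eight members, ICC 0.20 and no caseworker variance. The main-effect variance is 2(0.2 + 0.8/8)/20 = 0.030 (SE 0.173), and the interaction variance is 2 × 0.8(1/2 + 1/6)/20 = 0.0533 (SE 0.231). Adding a caseworker variance of 0.05 raises the main-effect variance by 2(0.05)/4 to 0.055 (SE 0.235) and leaves the interaction unchanged, so the order reverses.

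Finally, the plan never says which slopes are random, so it cannot be said to propose an impossible one. A role slope across CFTs or caseworkers could be legitimate.

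**Conclusion.** The concern holds as an inconsistency in the primary inference. The sentence naming the effect of primary interest conflicts with the sentence two before it and with the hypothesis, the mediation model and the power statement. Followed as written, it would give a null primary result for a uniform benefit of any size. This part needs no assumption about the sample.

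The second part is conditional. With the factor as the individual person, the interaction has 0 degrees of freedom under both sampling descriptions, provided members do not cross arms. With the factor as a role present in both arms, it is estimable but remains unhypothesized and without stated power. Under either reading it cannot apply to service linkage or to the three single-arm measures. No claim is made that the interaction is inherently the weaker test.

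**What to change.** - Name the condition main effect as the primary test, with random intercepts for CFT and caseworker.
- Define the participant factor as member role, for example parent/caregiver, caseworker, other formal support and informal support. The Demographics section lists working status/profession but not CFT role, so add a role item to the survey if it is not already captured.
- Make condition × role a secondary analysis and report the parent/caregiver contrast from it, since the stated aims centre on family voice and parental satisfaction.
- Drop any random slope for individual person within a meeting, or for condition within caseworker or CFT. A random slope for role may stay in the secondary model where it can be estimated; omitting it could understate the standard error of the interaction if role effects vary between clusters.
- State that service linkage is analysed per child by condition, and that the feasibility, acceptability and appropriateness measures are summarized within CFT + AAR only.

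The cost is a few sentences in the Analytic plan and at most one survey item. The design and the sample size do not change.
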